### Randomization

2.3

A stratified block randomization method will be employed in this study. Participants will be randomly assigned to the following three groups: MICT group (n=35), HIIT group (n=35), and LHIIT group (n=35). Stratification is based on sex (male and female) and age. Stratification will be based on participant gender (Male, Female) and age group (18–30 years and 31–45 years), resulting in four distinct strata. Within each stratum, a computer-generated randomization sequence will be created using permuted blocks of size 6. The randomization list was generated prior to study commencement using R 4.5.1. To ensure allocation concealment, sequentially numbered, opaque, sealed envelopes will be prepared in advance based on the stratified randomization list. Following eligibility confirmation and informed consent, the research coordinator allocated the participant to the treatment group indicated in the next available envelope within the appropriate stratum.

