### Research design

2.1

This trial is a single-center, three-arm, open-label randomized controlled study (**Figure 1**). As a superiority trial, a non-exercise control group will not be included, given that numerous studies have already demonstrated the significant efficacy of aerobic training for decreasing HFC in individuals with MASLD. A total of 105 eligible participants aged 18–45 years will be randomized in a 1:1:1 ratio to the high-intensity interval training (HIIT) group, moderate-intensity continuous training (MICT) group, or low-volume HIIT (LHIIT) group. The intervention will last 12 weeks. The HIIT and MICT groups will perform exercise sessions aiming for approximately 400 kcal per session (~1200 kcal/week), while the LHIIT group will perform shorter sessions of approximately 200 kcal per session. To minimize confounding factors, all participants will receive standardized dietary guidance to maintain a stable caloric intake consistent with their baseline habits during the intervention period. All exercise sessions will be supervised by certified exercise trainers to ensure adherence, safety, and fidelity to the protocol. Due to the nature of the interventions, participants and trainers cannot be blinded; however, outcome assessors, imaging analysts, and statisticians will remain blinded to allocation. The primary outcome is the change in HFC, quantified by magnetic resonance imaging–proton density fat fraction (MRI-PDFF), with the primary comparison set between HIIT and MICT. Analyses involving the LHIIT group are considered exploratory and will be interpreted as hypothesis-generating. This trial protocol has been reviewed and approved by the Ethics Committee of the First Affiliated Hospital of Naval Medical University (CHEC2025-253) and registered on the Chinese Clinical Trial Registry (ChiCTR2500107821). Any modifications to the protocol will be fully documented and described in detail in subsequent publications.

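### One fixed, published block size of 6 within four easily tracked strata of an open-label, single-centre trial leaves about 18% of allocations deducible with certainty; varying the size is a cheap improvement

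*Protocol article*

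**What the plan says.** Section 2.3 (Randomization) describes stratified block randomisation by sex and "age group (18–30 years and 31–45 years), resulting in four distinct strata". On how the list is built, it states that "a computer-generated randomization sequence will be created using permuted blocks of size 6". No other size and no variation in size is mentioned. For concealment, "sequentially numbered, opaque, sealed envelopes will be prepared in advance based on the stratified randomization list". After eligibility is confirmed and consent given, "the research coordinator allocated the participant to the treatment group indicated in the next available envelope within the appropriate stratum".

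Section 2.1 (Research design) sets the context: "This trial is a single-center, three-arm, open-label randomized controlled study", with participants "randomized in a 1:1:1 ratio to the high-intensity interval training (HIIT) group" and two other arms. On blinding it says that "participants and trainers cannot be blinded; however, outcome assessors, imaging analysts, and statisticians will remain blinded to allocation".

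Section 2.2 (Subjects) schedules recruitment from January 2026 to January 2028. Investigators screen medical records and research staff invite eligible people to consent.

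**The concern.** A block of 6 for three arms at 1:1:1 contains two HIIT, two MICT and two LHIIT places. Once the size is known, assignments already made in a block narrow down those still to come. Four features make the deduction practicable here: the size is single and published, assignments are open once made, there is one site, and the strata depend only on sex and an age band known at screening.

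Opaque envelopes hide the next slip but not the arithmetic. Opening the envelope after consent does not help either, because a forecast made from the block is available before anyone is invited. A person who both recruits and knows the tally could delay or discourage an invitation according to how fit or motivated a candidate seems. The arms differ in demand (section 2.5: 45–55% of heart rate reserve for MICT, work intervals at 70–90% for HIIT), so such selection could distort the primary HIIT versus MICT comparison. Blinded MRI protects the measurement of liver fat, not the choice of who enters each arm.

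**Working it through.** The article gives no predictability figure to reproduce, so the check starts from its stated rule.

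**Inputs.** Block size 6 and four strata (section 2.3); three arms at 1:1:1 (section 2.1); 105 participants (section 2.6). The stratum sizes are not given. Even strata of about 26 are my assumption, and I show the range over all other splits.

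**Step 1: one complete block.** There are 6!/(2!·2!·2!) = 90 equally likely orders. For each position, given the assignments before it:

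| Position | Arm certain | At least one arm ruled out | Best guess correct |
|---|---|---|---|
| 1 | 0 | 0 | 0.333 |
| 2 | 0 | 0 | 0.400 |
| 3 | 0 | 0.2 | 0.500 |
| 4 | 0 | 0.6 | 0.533 |
| 5 | 0.2 | 1 | 0.600 |
| 6 | 1 | 1 | 1.000 |
| Sum | 1.2 | 2.8 | 3.367 |

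Position 5 is certain when the last two places belong to the same arm: 3 × 6/90 = 0.2. Divided by 6, the sums give 20% certain, 46.7% with an arm ruled out, and 56.1% best-guess success, against 33.3% by chance.

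**Step 2: this trial.** Final blocks may be incomplete. The expected number of certain allocations is 1.2 × (complete blocks) + 0.2 × (final blocks that stop at five).
- Strata of 26, 26, 26 and 27 have 4 complete blocks each: 16 × 1.2 = 19.2, and 19.2/105 = 18.3%.
- Over all splits of 105 into four strata, the minimum is 15 × 1.2 = 18.0 (17.1%) and the maximum is 17 × 1.2 = 20.4 (19.4%).

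**Step 3: present scheme in a stratum of 26** (four complete blocks plus two places).
- Certain: 4 × 1.2/26 = 18.5%.
- Arm ruled out: 4 × 2.8/26 = 43.1%.
- Best guess: (4 × 3.367 + 0.333 + 0.400)/26 = 14.2/26 = 54.6%.

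**Step 4: varying sizes on the same footing.** This was simulated in strata of 26. Sizes are drawn with equal probability, and the observer knows the set of sizes but not their order and updates by Bayes' rule after each assignment.

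| Sizes | Certain | Arm ruled out | Best guess correct |
|---|---|---|---|
| 6 only | 18.5% | 43% | 54.6% |
| 6, 9 | about 5% | 13% | 52.7% |
| 3, 6, 9 | about 3% | 9% | 53.9% |

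The change removes most of the certainty. It removes little of the average guessability.

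**Step 5: cost in power.** Section 2.6 uses a difference of 0.8, SD 0.92, two-sided α = 0.05 and 28 per group. Power = Φ(0.8/[0.92·√(1/28 + 1/28)] − 1.96) = 90.2%, which reproduces the stated 90%. With 26 and 30 instead of 28 and 28, the same formula gives 90.1%.

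**The case against.** The strongest reply is that this is an opportunity that nobody is shown to have. The article does not say that recruiters see a running tally, that the research coordinator recruits, or that only one person fills that role. Investigators screen, research staff invite, and the coordinator opens envelopes after consent. Trainers are unblinded, but they work at a community fitness centre and are given no part in recruitment. All of this stands, and it limits the point to what could happen. A reader might infer that HIIT versus MICT will be biased, but the documents do not support that: they give no basis for the size, the direction or even the presence of selection.

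A second reply is that the proposed change hardly alters overall guessability. This also stands. Someone steering enrolment can act on a probable arm as well as a certain one, and best-guess success drops by only about two percentage points with sizes 6 and 9. A reader who saw only the fall in certain allocations might infer that predictability as a whole collapses, and it does not.

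Third, other protections exist: numbered opaque envelopes, assignment after consent, blinded MRI acquisition and analysis, and an ANCOVA with baseline liver fat as covariate (section 2.7). These limit the harm. The ANCOVA would largely deal with selection on baseline liver fat, but not with selection on motivation or expected adherence.

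Fourth, a reader might infer that the list was made by someone involved in enrolment. The article does not say who made it, and a condensed article may leave that to the full protocol, so it is no part of this point. The block size is different, because the article fixes it.

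**Conclusion.** The point holds as a cheap improvement. Under the stated rule, about 18% of allocations (17% to 19%, depending on the stratum sizes) could be known in advance, and at least one arm could be ruled out for about 43%, by anyone who tracks assignments by stratum. This rests on the published single size of 6, on complete tracking by the observer, and, for the 43%, on strata of about 26. If nobody involved in enrolment sees the tally, the practical effect is nil. If someone does, the safeguards in the article reduce the scope for selection bias in HIIT versus MICT but do not close it, and the planned analysis could not fully undo it afterwards. There is no error of arithmetic or contradiction in section 2.3; the weakness is a rule that gives away more than it needs to.

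**What to change.** Keep the four strata and the envelopes. Regenerate the unopened part of the list in R with block sizes drawn at random, preferably from 6 and 9, starting at the next unopened envelope in each stratum. Do not disclose the new sizes or their order to recruiting staff until recruitment ends; until then, section 2.3 need say only that block sizes vary at random. Sizes 6 and 9 are preferred to 3, 6 and 9 because they give the lower best-guess success (52.7% against 53.9%), with nearly as few certain allocations. Record the change, as section 2.1 already promises for any modification.

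The cost is a few lines of code and a new set of envelopes. An incomplete final block can leave two arms up to 3 apart in a stratum with size 9, against 2 with size 6. The present scheme does not guarantee 35 per arm either, since 105 is not a multiple of 6. The effect on power is negligible, as the working shows.

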### Subjects

2.2

This study aims to recruit a total of 105 participants at the First Affiliated Hospital of Naval Medical University, with recruitment scheduled from January 2026 to January 2028. **Table 1** summarizes the detailed inclusion and exclusion criteria for participant selection. Recruitment will be facilitated through hepatology and weight management outpatient clinics at the hospital. Additionally, informational flyers will be distributed in community hospitals and health examination centers within a 5-kilometer radius of the main hospital to expand outreach efforts. Potential participants will be initially screened through review of their electronic medical records by study investigators to assess eligibility. Eligible individuals will then be invited to provide written informed consent by research staff, followed by completion of baseline assessments within four weeks of enrollment.

**Table 1 T1:** Inclusion and exclusion criteria.

Inclusion criteria
- Age between 18 and 45 years, with no restrictions on gender
- Meets the diagnostic for MASLD
- Medication type and dosage have remained stable over the past three months
- No regular exercise routine(3 sessions/week, 30 minutes/session)
Exclusion criteria
- Weight change exceeding 5% in the past three months
- Inability to maintain blood glucose and blood pressure within normal ranges despite standard treatment
- Inability to participate in exercise testing and training due to any condition
- Women who are pregnant, planning to conceive, or in the periconceptional period
- Currently undergoing any form of hormone therapy.

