### Assessments and procedures

2.4

All study outcomes and corresponding assessment time points are presented in **Table 2**. The primary outcome is the change in HFC, as measured by magnetic resonance imaging, from baseline to 12 weeks post-intervention. Secondary outcomes encompassed: (1) anthropometric parameters; (2) body composition and abdominal fat; (3) cardiorespiratory fitness; (4) cardiometabolic biomarkers; and (5) Indicators of liver inflammation and fibrosis. Detailed measurement procedures are described below.

**Table 2 T2:** The study schedule.

Study phase	Screening	0 week	4 week	8 week	12 week
Informed consent	✓	–	–	–	–
Demographics	✓	–	–	–	–
Medical history	✓	–	–	–	–
Lifestyle counseling	✓	✓	✓	✓	✓
Medications report	✓	✓	✓	✓	✓
Physical and diet assessment	✓	✓	✓	✓	✓
Anthropometric assessment	✓	✓	✓	✓	✓
Randomization	✓	–	–	–	–
MRI-PDFF	–	✓	–	–	✓
Cardiometabolic biomarkers	✓	✓	–	–	✓
Liver inflammatory biomarkers	✓	–	–	–	✓
Body composition	✓	✓	–	–	✓
Cardiorespiratory fitness	✓	✓	–	–	✓
Quality of life	✓	✓	–	–	✓
Adherence	✓	✓	✓	✓	✓
AEs	✓	✓	✓	✓	✓

MRI-PDFF, Magnetic Resonance Imaging - Proton Density Fat Fraction; AEs, adverse events.

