#### Primary outcomes

2.4.1

The primary outcome is the absolute change in HFC, quantified as MRI-PDFF, from baseline to 12 weeks. All MRI-PDFF measurements will be acquired using a standardized multi-echo gradient-echo sequence on the same 3.0T scanner (Magnetom Prisma, Siemens Healthineers, Erlangen, Germany), using an 18-channel body and a 32-channel spine phased-array coil, conducted by a single professional technician who is blinded to group allocation. A multi-echo 3D spoiled gradient-echo sequence (Volumetric Interpolated Breath-hold Examination-Based, VIBE) integrated within the Siemens LiverLab sequence will be performed under a single end-expiratory breath-hold. Typical acquisition parameters included: repetition time (TR)< 12 ms, six asymmetric echo times (TEs, e.g., first TE ~1.2ms, echo spacing ~1.2ms), flip angle ~3-6°, axial orientation, field of view covering the entire liver, and parallel imaging. PDFF maps will be automatically generated by LiverLab, which employs a multi-peak fat spectral model and corrects for T2-weight decay. The liver will be segmented using an artificial intelligence algorithm embedded in the assessment program. Segmentations with a goodness-of-fit exceeding 95% will be accepted after reviewing the images and reports.

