### Statistical analysis plan

2.7

Baseline characteristics and study outcomes will be summarized using descriptive statistics. The normality of continuous variables will be assessed using the Shapiro-Wilk test and visual inspection of histograms and Q-Q plots. Continuous variables with a normal distribution will be presented as means ± standard deviations (SD), while non-normally distributed variables will be reported as medians and interquartile ranges (IQR). Treatment effects will be reported as the estimated mean difference (MD) between groups with 95% confidence intervals (CIs) to provide a clear estimation of the effect size. Categorical variables will be expressed as frequencies and percentages (n, %). Baseline differences between groups will be assessed using one-way ANOVA or Kruskal-Wallis tests for continuous variables, and Chi-square tests or Fisher’s exact tests for categorical variables.

The analysis will be conducted according to the Intention-to-Treat (ITT) principle, including all randomized participants (N = 105) for both primary and secondary endpoints. To address missing data arising from participant withdrawal, Multiple Imputation by Chained Equations (MICE) (m=20 imputed datasets) will be performed prior to the primary analysis. Treatment effects will be evaluated using analysis of covariance (ANCOVA). The post-intervention measurements will be included as the dependent variable. Fixed effects will include group (HIIT, MICT, LHIIT), and the baseline measurements will be included as a covariate. The results from the imputed datasets will be pooled using Rubin’s rules. Tukey’s Honestly Significant Difference test will be used for *post-hoc* pairwise comparisons. Furthermore, sensitivity analyses for primary outcome will be conducted to assess the robustness of the results. These will include: (1) a Per-Protocol analysis; (2) an analysis excluding participants with >5% body weight change; and (3) an analysis including percentage body weight change as a covariate in the primary ANCOVA model. All statistical analyses will be performed using R software (version 4.5.1). A two-sided p-value< 0.05 will be considered statistically significant.

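### As written, the baseline MRI-PDFF, which is both the start of the primary outcome and the ANCOVA covariate, is taken after open-label allocation

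*Protocol article*

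**What the plan says.** Section 2.3 (Randomization) gives two steps that must come before the envelope is opened: "Following eligibility confirmation and informed consent, the research coordinator allocated the participant to the treatment group indicated in the next available envelope". It does not mention completed baseline measurements.

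Table 2 (section 2.4) shows the sequence. The row "Randomization" is ticked at Screening and dashed at week 0. The MRI-PDFF row is dashed at Screening and ticked at week 0 and week 12.

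Section 2.2 (Subjects) puts consent first, "followed by completion of baseline assessments within four weeks of enrollment".

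On blinding, section 2.1 says that "participants and trainers cannot be blinded; however, outcome assessors, imaging analysts, and statisticians will remain blinded to allocation". Section 2.4.1 adds that the scan is "conducted by a single professional technician who is blinded to group allocation".

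Section 2.4.1 defines the endpoint: "The primary outcome is the absolute change in HFC, quantified as MRI-PDFF, from baseline to 12 weeks". Section 2.7 fits an ANCOVA in which "the baseline measurements will be included as a covariate", in a set "including all randomized participants (N = 105) for both primary and secondary endpoints".

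**The concern.** A baseline covariate is safe to adjust for because allocation cannot have affected it. Once participants know their arm, that protection depends on nothing happening between the envelope and the scan. Two things could happen.

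- **Behaviour.** Someone who knows the arm may change activity or eating before the week-0 scan. The PDFF then recorded as baseline already carries some effect of allocation. Both the change score and the covariate adjustment inherit it.
- **Withdrawal.** Someone who does not want the assigned arm may leave before the scan. That person is randomised, so belongs to the intention-to-treat set, but has neither a baseline nor a week-12 PDFF. Multiple imputation must supply both values.

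There is also a practical consequence. Section 2.4.1 accepts a segmentation only above a goodness-of-fit threshold, so under this order an unusable baseline scan comes to light only after randomisation.

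The primary outcome is more exposed than most others. In Table 2, anthropometry, cardiometabolic and liver biomarkers, body composition, cardiorespiratory fitness and quality of life all have a Screening tick. MRI-PDFF has none. The MRI measure of abdominal fat, acquired at the same time as the liver scan (section 2.4.2.2), shares the problem.

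**Working it through.** The point concerns the order of steps, so the main check is to set the places side by side.

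| Place | What it fixes |
|---|---|
| Section 2.2 | Consent, then baseline assessments, with a limit counted from enrolment |
| Section 2.3 | Envelope opened after eligibility and consent; MRI not a condition |
| Table 2 | Randomisation at Screening; first MRI-PDFF at week 0 |
| Section 2.1 | Participants and trainers know the arm; assessors, imaging analysts and statisticians do not |
| Section 2.9 | Physicians carry out baseline health assessments to confirm eligibility; MRI not named |

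The table and section 2.3 are consistent with each other. Nothing in the article puts the MRI before allocation.

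**The plan's own figure.** Inputs from section 2.6: reductions of 1.7 (SD 1.1) and 0.9 (SD 0.7), two-sided α = 0.05, power 90%, dropout 20%.

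- Difference = 1.7 − 0.9 = 0.8.
- Pooled SD = √((1.1² + 0.7²)/2) = √0.85 = 0.922, stated as 0.92.
- n = 2(1.960 + 1.282)² × 0.92² / 0.8² = 27.8, so 28 per group.
- 28/(1 − 0.20) = 35 per group, and 3 × 35 = 105.

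The sample size reproduces and the order of steps does not affect it.

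**Illustration only.** The inputs below are assumptions with no support in the document. Let *b* be the HIIT–MICT difference in PDFF that has already arisen and persists when the week-0 scan is taken, and let β be the ANCOVA slope on baseline. If the total difference from allocation to week 12 is 0.8 and HIIT participants moved first, the adjusted difference is 0.8 − β*b*. Power is for a two-sample t-test with 28 per group and SD 0.92; with no shift it is 0.89.

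| *b* | β | Adjusted difference | Power |
|---|---|---|---|
| 0.1 | 0.7 | 0.73 | 0.83 |
| 0.1 | 1.0 | 0.70 | 0.80 |
| 0.2 | 0.7 | 0.66 | 0.75 |
| 0.2 | 1.0 | 0.60 | 0.67 |
| 0.3 | 0.7 | 0.59 | 0.65 |
| 0.3 | 1.0 | 0.50 | 0.52 |

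If MICT participants moved first, the sign reverses and the difference is inflated, from 0.8 + 0.7 × 0.1 = 0.87 up to 0.8 + 1.0 × 0.3 = 1.10. The table shows the mechanism. It does not estimate what will happen in this trial.

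**Withdrawal.** Each participant lost between envelope and scan is 1 of 35 in the arm (2.9%) with no primary-outcome data. The document gives no basis for an expected number.

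**The case against.** The best defence is that Table 2 is loosely filled in. It ticks adherence at Screening, before any session exists. It shows no cardiorespiratory test at weeks 4 and 8, although section 2.5 repeats the CPET then. It lists quality of life, which is not among the secondary outcomes named in section 2.4. The randomisation tick may therefore be clerical. Section 2.9 shows that some baseline assessment precedes eligibility, and the flow figure is not available here. All of this stands as a reason not to assert that the trial is actually being run in this order. It does not remove the point: section 2.9 does not name the MRI, section 2.3 does not correct the table, and a wrong tick in a schedule still needs correcting.

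A reader might infer that participants know their arm for up to four weeks before the scan. The document does not support that. Section 2.2 counts from enrolment, does not equate enrolment with randomisation, and gives no interval between allocation and scan, which could be very short.

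A reader might also infer a bias of known size, for example 0.1 to 0.2 points, which is 12.5% to 25% of the planned 0.8. Those shifts are assumed. HIIT and MICT share the same target energy per session, and all participants receive the same dietary guidance, so a difference between these two arms before training may be small.

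Finally, blinded imaging staff and automated PDFF make measurement bias unlikely. That is correct, but it does not prevent changes in behaviour or withdrawal. The 20% dropout allowance and multiple imputation soften the loss of information, and screening measurements could inform the imputation. Neither removes selective withdrawal.

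**Conclusion.** The concern holds for the schedule as written: the baseline of the primary outcome follows an open-label allocation, and no text requires otherwise. The routes to bias are differential behaviour and selective withdrawal before the scan. Size and direction cannot be derived from the document, and no sample-size figure is affected. The conclusion rests on taking Table 2 and section 2.3 at their word. If the tick is a clerical error, the design is sound but the document still needs correcting. Because the exposed measurement serves the single primary comparison and the remedy only reorders existing steps, the change should be made.

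**What to change.** In Table 2, move the randomisation tick to week 0, placed after the MRI-PDFF. In section 2.3, state that the envelope is opened only after the week-0 baseline assessments are complete, including an MRI-PDFF that meets the segmentation criterion, and before the first training session.

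If the present order is intended, say so, and state how a missing baseline PDFF is handled. If participants have already been randomised in that order, report by arm the interval from allocation to scan and the number with no baseline PDFF.

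The cost is small. No procedure is added and the sample size does not change. A few people will be scanned and then not randomised.
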